#### Patient-reported quality of life

Health-related quality of life data will be analysed using version 3 of the *European Organisation for Research and Treatment of Cancer* (EORTC) QLQ-C30 Scoring Manual (2001) in all dimensions. Results will be presented for the global health status/QoL score, functional and symptom dimensions, and for individual items.

### Statistical analysis

#### Sample size calculation

As the total number of available lesions will depend on how many lesions per patient are treated, several scenarios were used to calculate the required sample size to achieve sufficient precision for analysis. Based on previously published data [11, 16], local tumour control rates of 60%, 70%, and 80% for 1, 1.5, and 2 tumours per patient were chosen as possible scenarios. Using the resulting sample size, the expected precisions were calculated using the two-sided 95% confidence interval according to the Wilson score method [20, 21].

A sample size of 500 patients with a median of 1.5 tumours per patient produces a two-sided 95% confidence interval with a precision equal to 0.057 when the sample proportion is 0.8.

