**Methods:**

Eligible patients are adults with up to 9 local treatment naïve CRLM of ≤ 3 cm completely treatable with either MWA alone or MWA with resection and/or radiotherapy within 8 weeks. Data are collected, at baseline, every 3 months until 12 months, and thereafter every 6 months until the end of the study. The primary outcome measure is local tumour control. Secondary outcome measures are overall survival, (hepatic-) disease-free survival, time-to-progression untreatable by ablation, systemic therapy vacation, safety, and quality of life. Covariates related to the primary outcome measure will be assessed using a stratified log-rank test and an univariable Cox proportional hazard regression. A sample size of 500 patients with 750 lesions produces a two-sided 95% confidence interval with a precision equal to 0.057.

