#### Outcome measures

The median time to event and 95% confidence interval will be calculated using the Kaplan–Meier estimator. Results will be illustrated graphically using Kaplan–Meier plots and the impact of different covariates will be assessed using a stratified log-rank test and an univariable Cox proportional hazard regression. The pre-defined list of covariates can be found in Supplement 1. Covariates that have at least a 10–90% ratio and no more than 10% missing data will be used. Covariates with *p* values of < 0.1 will be included in a multivariable Cox proportional hazard regression model. Backwards elimination will be used for model building. The criteria for retaining variables in the model based on statistical significance (*p* < 0.05) and model improvement. The Cox proportional hazard assumptions will be verified and covariates that do not satisfy those assumptions will be flagged.

Quality of life outcomes will be presented by absolute values and change from baseline using summary statistics. Summaries will be broken down into subgroups and covariate analyses may be performed using analysis of covariance (ANCOVA) depending on the number of available questionnaires at the final analysis.

All statistical tests will be based on a significance level of 5%, and estimates will be presented using two-sided 95% confidence intervals. As it is not planned to test any statistical hypotheses in a confirmatory sense, statistical testing will have to be interpreted in the perspective of the study.

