## Current status of the study

Between October 2018 and June 2022, 100 hospitals that met the selection criteria were invited, of which 36 were activated (by means of training, access to the database, and eligibility to include patients). As of January 2023, 500 patients have been enrolled with 976 treated tumours, achieving the minimum sample size of 976 lesions for a precision between 0.04 and 0.06. Follow-up data will be collected until January 2026. The final clinical outcome results are expected to be published by 2027.

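### The stated precision counts every lesion as independent, although the primary outcome is per lesion and 976 lesions lie in 500 patients

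*Protocol article*

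**What the plan says.** Table 2 of the Protocol article defines the primary outcome as local tumour control at 12 months, counted per lesion. Table 1 allows up to 9 liver lesions per patient.

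Under Sample size calculation, "local tumour control rates of 60%, 70%, and 80% for 1, 1.5, and 2 tumours per patient were chosen as possible scenarios", and "the expected precisions were calculated using the two-sided 95% confidence interval according to the Wilson score method". The headline result is that a sample of 500 patients with "a median of 1.5 tumours per patient produces a two-sided 95% confidence interval with a precision equal to 0.057", for a sample proportion of 0.8. The abstract gives the lesion count behind it: "A sample size of 500 patients with 750 lesions produces a two-sided 95% confidence interval with a precision equal to 0.057".

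Under Current status of the study, "500 patients have been enrolled with 976 treated tumours", with a stated precision between 0.04 and 0.06. The Discussion gives 0.04–0.07 for at least 803 lesions and, on that basis, calls the reduced sample statistically sufficient.

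The Time-to-event section plans per-lesion analyses that start at the first ablation of the respective lesion. Under Outcome measures, "the impact of different covariates will be assessed using a stratified log-rank test and an univariable Cox proportional hazard regression". Covariates with p < 0.1 then enter a multivariable Cox model with backward elimination. No ICC, design effect, patient cluster term or frailty is mentioned.

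**The concern.** Lesions in one patient share tumour biology, systemic treatment and treating centre, so their outcomes are likely to be positively correlated. Follow-up is shared too: under Missing data, a death before 12 months turns all of that patient's lesions without determined progression into drop-outs together. Two correlated lesions carry less information than two lesions from different patients, so a binomial interval on the lesion count is too narrow.

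This bears on the primary estimate, whose confidence interval is the main inferential result of a single-arm study, and on the precision used to justify going from 700 to 500 patients. It could also affect the search for factors linked to local control, which the Conclusion names as an aim. If a patient-level covariate is tested as though each lesion were a separate patient, its standard error is too small.

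**Working it through.** **Inputs from the article.** 500 patients; 750 planned lesions (500 × 1.5); 976 accrued lesions (mean m = 976/500 = 1.952); control rates of 60%, 70% and 80%; two-sided 95% level, z = 1.96.

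**Inputs assumed.** The article gives no ICC and no spread of lesions per patient. I use ICC 0.1, 0.2 and 0.3, and either equal cluster sizes (CV 0, the most favourable case) or CV 0.8.

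**Step 1: reproduce the stated figures.** The full width of the Wilson interval is

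W(n, p) = 2z·√[p(1−p)/n + z²/(4n²)] / (1 + z²/n).

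- n = 750, p = 0.8: W = 0.0572, which is the stated 0.057. The half-width is 0.0286, so precision here means full width. The article does not say so.
- n = 500, p = 0.8: W = 0.0700. The stated figure therefore uses lesions, not patients, as n.
- n = 976, p = 0.6 / 0.7 / 0.8 / 0.9: W = 0.061 / 0.057 / 0.050 / 0.038, matching the stated 0.04 to 0.06 after rounding.
- n = 803, same rates: W = 0.068 / 0.063 / 0.055 / 0.042, matching the stated 0.04–0.07.

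The lower limit of 0.04 is reached only at about 90%, a rate not among the three listed scenarios. All the figures follow from plain lesion counts with no allowance for clustering.

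**Step 2: apply a design effect.** DE = 1 + [(1 + CV²)·m − 1]·ICC, and n_eff = n/DE. For example, with 750 lesions, CV 0 and ICC 0.2: DE = 1 + 0.5 × 0.2 = 1.10, n_eff = 682, W = 0.0600.

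| Lesions, rate | Independent | CV | ICC 0.1 | ICC 0.2 | ICC 0.3 |
|---|---|---|---|---|---|
| 750, 80% | 0.0572 | 0 | 0.0586 | 0.0600 | 0.0613 |
| 750, 80% | 0.0572 | 0.8 | 0.0612 | 0.0650 | 0.0685 |
| 976, 80% | 0.0501 | 0 | 0.0525 | 0.0547 | 0.0568 |
| 976, 80% | 0.0501 | 0.8 | 0.0554 | 0.0602 | 0.0646 |
| 976, 60% | 0.0614 | 0 | 0.0642 | 0.0669 | 0.0695 |
| 976, 60% | 0.0614 | 0.8 | 0.0677 | 0.0736 | 0.0790 |

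**Step 3: is 0.057 still met with the accrued lesions?** At 80% it is, as long as n_eff ≥ 750, that is DE ≤ 976/750 = 1.30. This limit is reached at ICC = 0.301/0.952 ≈ 0.32 with equal clusters, and at ICC = 0.301/(1.64 × 1.952 − 1) ≈ 0.14 with CV 0.8.

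**Step 4: covariate tests, if the variance were left naive.** For a covariate that is constant within a patient, the actual level of a nominal 5% test is roughly 2·[1 − Φ(1.96/√DE)]. At 976 lesions and ICC 0.1 / 0.2 / 0.3, DE is 1.095 / 1.190 / 1.286 with equal clusters, giving 6.1% / 7.2% / 8.4%. With CV 0.8, DE is 1.220 / 1.440 / 1.660, giving 7.6% / 10.2% / 12.8%. This is an approximation carried over from the design effect for a proportion.

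**The case against.** The strongest reply is that only the planning figure is shown to assume independence. The Wilson method is named for expected precision, and the article does not fix the method for the final interval. A cluster-robust variance or a frailty term is the kind of detail often left to the full protocol or the SAP, neither of which is shown. The log-rank test is described as stratified, with strata not named. All of this stands. A reader might infer that the final primary interval will undercover, or that the per-lesion Cox and log-rank tests do treat lesions as independent. The article's silence does not establish either.

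The planned figure also moves little: from 0.057 to 0.059–0.061 for ICC 0.1 to 0.3 with equal clusters. More lesions were accrued than planned, so 0.057 at 80% may well still be met. A reader might infer that the sample is inadequate; the figures do not show that.

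Finally, the article declares its testing non-confirmatory, which lowers the stakes for the covariate analyses. A reader might also conclude that all p-values will be too small. That holds only for covariates constant within a patient. For covariates that differ between lesions of one patient, such as lesion size, a naive test can err in either direction. Per-patient outcomes such as overall and disease-free survival are not touched.

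None of this rescues the published precision figures, which reproduce from plain lesion counts and which an unseen SAP cannot change.

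**Conclusion.** The point holds for the precision statements, with high confidence, because it follows from reproducing the article's own numbers. The figures for 750, 976 and 803 lesions are full widths that ignore clustering of lesions within patients, and they are too narrow under any positive within-patient correlation.

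At 80% control and an assumed ICC of 0.1 to 0.3, the understatement is modest: about 0.001 to 0.004 of full width for 750 lesions with equal clusters, and up to about 0.011 with CV 0.8. At 60% control, the width for 976 lesions becomes 0.064–0.079 across both CV assumptions, above the stated upper limit of 0.06. It is already 0.061 under independence.

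For the per-lesion covariate analyses confidence is lower. The article names the methods without a patient cluster term, so the request is to confirm or add one. Overall this should be fixed, but it does not undermine the study.

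**What to change.** 1. Restate the expected precision, saying that it is the full width of the 95% confidence interval. Apply the design effect 1 + [(1 + CV²)·m − 1]·ICC over a stated ICC range, with m and CV taken from the accrued lesions-per-patient distribution.
2. Report the primary local-control rate with a patient-clustered confidence interval, by cluster bootstrap or by GEE with sandwich variance.
3. For per-lesion time-to-event analyses, confirm or add robust standard errors clustered on patient, or a shared patient frailty. Use the corresponding robust test for the p < 0.1 screen and the backward elimination, and name the strata of the log-rank test.

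No new data are needed. Follow-up runs to January 2026 and results are expected by 2027, so there is time. The cost is some wording, minor extra coding and a slightly less favourable stated precision.

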#### Outcome measures

The median time to event and 95% confidence interval will be calculated using the Kaplan–Meier estimator. Results will be illustrated graphically using Kaplan–Meier plots and the impact of different covariates will be assessed using a stratified log-rank test and an univariable Cox proportional hazard regression. The pre-defined list of covariates can be found in Supplement 1. Covariates that have at least a 10–90% ratio and no more than 10% missing data will be used. Covariates with *p* values of < 0.1 will be included in a multivariable Cox proportional hazard regression model. Backwards elimination will be used for model building. The criteria for retaining variables in the model based on statistical significance (*p* < 0.05) and model improvement. The Cox proportional hazard assumptions will be verified and covariates that do not satisfy those assumptions will be flagged.

Quality of life outcomes will be presented by absolute values and change from baseline using summary statistics. Summaries will be broken down into subgroups and covariate analyses may be performed using analysis of covariance (ANCOVA) depending on the number of available questionnaires at the final analysis.

All statistical tests will be based on a significance level of 5%, and estimates will be presented using two-sided 95% confidence intervals. As it is not planned to test any statistical hypotheses in a confirmatory sense, statistical testing will have to be interpreted in the perspective of the study.

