### Data collection and quality control

Patients enter the study by accepting participation and signing the informed consent form. Baseline data are collected one month prior to the first treatment (see Fig. 1). Additionally, the relevant data to calculate the baseline Charlson Comorbidity Index (CCI) and the clinical risk score (Fong Score) are collected [18, 19]. After each treatment, technical parameters are collected on how the treatment is performed, whether simultaneous resection of other lesions is performed, and whether concomitant systemic therapy is received. Follow-up data are collected 1 month after the treatment, then every 3 months for the first 12 months and then every 6 months until the study exit or study end, 36 months after the 500th patient has been included. Data for safety and adverse events are collected throughout the whole study. HRQOL data are collected before the first treatment and at the first follow-up.

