### Primary outcome measure

The primary outcome measure is the local control rate for all ablated tumours at 1 year (defined as fully ablated with no evidence of disease within the ablation zone at 12 months + / − 45 days after the last ablation of the respective tumour) as assessed by the investigatorsʼ routine protocols (Table 2).

**Table 2 Tab2:** Primary and secondary outcome measures

	Outcome measure	Measured according to	Definition
*Primary outcome measure*			
Effectiveness	Local tumour control at 12 months on a per lesion basis	Investigator assessment	Tumour is considered to be fully ablated with no evidence of disease within the ablation zone at 12 months + / − 45 days after the last ablation
*Secondary outcome measures*			
Safety	Adverse events	CTCAE V5.0	
Effectiveness	Overall survival	Investigator assessment	Time between the first treatment and the time of death of any cause
	Overall disease-free survival	Investigator assessment	Time between the first treatment and the time of any progression, new tumours, or death
	Hepatic disease-free survival	Investigator assessment	Time between the first treatment and the time of any progression of hepatic tumours, new hepatic tumours or death
	Time to untreatable progression by thermal ablation	Investigator assessment	Time between the first treatment and the time of progression of a treated tumour that has been determined as not treatable by thermal ablation
	Systemic cancer therapy vacation	Investigator assessment	Time between the first treatment and the start of systemic cancer therapy
	Quality of Life	EORTC QLQ-C30	

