#### Time-to-event

The first MWA treatment will be the starting point for the per-patient time-to-event analyses, and the first MWA treatment of the respective lesion for per-lesion time-to-event analyses. OS is defined as the time of death of any cause, for DFS as the time of any progression, new tumours, or death, for HDFS as the time of any progression of liver tumours, new tumours in the liver or death and for time to progression untreatable by thermal ablation as the time of progression of a treated tumour that has been determined as not treatable by thermal ablation according to the investigator. Systemic cancer therapy vacation is defined as the time between the first MWA treatment and the start of systemic cancer therapy. In these analyses, subjects lost to follow-up will be censored at the last recorded communication with the patient.

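### Kaplan-Meier is fixed for two secondary outcomes whose definitions leave out death, so the reported probability of the event would be too high and the median too short

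*Protocol article*

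**What the plan says.** The Outcome measures part of the Statistical analysis section states "The median time to event and 95% confidence interval will be calculated using the Kaplan–Meier estimator" and adds Kaplan-Meier plots. It makes no exception by outcome. The effect of covariates "will be assessed using a stratified log-rank test and an univariable Cox proportional hazard regression", followed by a multivariable Cox model. No competing-risk method is named.

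The event definitions are in Table 2 and in the Time-to-event section:

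- Disease-free survival: "Time between the first treatment and the time of any progression, new tumours, or death".
- Hepatic disease-free survival: "Time between the first treatment and the time of any progression of hepatic tumours, new hepatic tumours or death".
- Time to untreatable progression: "Time between the first treatment and the time of progression of a treated tumour that has been determined as not treatable by thermal ablation".
- Vacation: "Systemic cancer therapy vacation is defined as the time between the first MWA treatment and the start of systemic cancer therapy".

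Death is therefore an event in the first two, as it is in overall survival, and is absent from the last two. The Time-to-event section gives a censoring rule for loss to follow-up only. The Missing data section says what happens when a patient dies, but only for the 12-month primary outcome.

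Data collection and quality control says that, after each treatment, the registry records "whether concomitant systemic therapy is received". Ongoing systemic therapy is not among the exclusion criteria in Table 1.

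**The concern.** A patient who has died can no longer show untreatable progression or start systemic therapy. Kaplan-Meier has only two states, event or censored, and it treats a censored patient as still able to have the event later. If deaths are censored, the curve describes a setting in which nobody dies, and it also requires death to be unrelated to the event. It does not give the share of registry patients who actually have the event by a given time, which is what a real-world registry would be expected to report.

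A smaller question concerns vacation. The clock starts at the first ablation and stops at a start of systemic therapy. For a patient already on therapy at the first ablation, the definition does not say whether the time is zero, runs to a later line of treatment, or is not counted at all.

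**Working it through.** **Figures in the plan.** The article states no rate, precision or expected median for these two outcomes. Its stated precision of 0.057 belongs to the primary outcome. It reproduces as the full width of the Wilson interval for 750 lesions and a proportion of 0.8 (0.0572), and it is not in dispute here.

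**Inputs, all assumed.** Constant hazards; probability of the event by 3 years with death censored, e, of 10-70%; probability of death without the event by 3 years, d, of 10-50%. The yearly hazards are a = -ln(1 - e)/3 for the event and b = -ln(1 - d)/3 for death.

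**Formulas.**
- One minus Kaplan-Meier, deaths censored: 1 - exp(-a·t).
- Cumulative incidence, death competing: a/(a + b) × [1 - exp(-(a + b)·t)].

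**Worked case, e = 30%, d = 20%, t = 3 years.** a = 0.1189 and b = 0.0744. One minus Kaplan-Meier is 30.0%. Cumulative incidence is 0.1189/0.1933 × (1 - 0.70 × 0.80) = 0.615 × 0.44 = 27.1%.

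**Cumulative incidence at 36 months:**

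| 1 - KM | death 10% | death 20% | death 35% | death 50% |
|---|---|---|---|---|
| 10.0% | 9.5% | 9.0% | 8.2% | 7.3% |
| 30.0% | 28.6% | 27.1% | 24.7% | 22.1% |
| 50.0% | 47.7% | 45.4% | 41.6% | 37.5% |
| 70.0% | 67.1% | 64.1% | 59.3% | 53.9% |

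The gap runs from 0.5 points (10.0 against 9.5) to 16.1 points (70.0 against 53.9).

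**At 12 months.** The largest gap on the grid is at e = 70%, d = 50%: 33.1% against 29.7%, which is 3.3 points before rounding.

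**Median.** With e = 50% the Kaplan-Meier median is 3.0 years. The cumulative incidence reaches 50% at 3.2, 3.5 and 4.4 years for d = 10%, 20% and 35%, and never for d = 50%. With e = 70% the Kaplan-Meier median is 1.73 years, against 1.80, 1.89, 2.08 and 2.45 years.

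**Orientation on mortality.** The Introduction cites 38% survival at 5 years after surgery. Under a constant hazard that is -ln(0.38)/5 = 0.194 per year, or about 44% dead by 3 years. This is another population and counts all deaths, so it shows only that the upper part of the assumed range is not far-fetched.

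**Vacation, patients already on therapy.** Assume a 12-month median among patients off therapy, a share f of 10-30% already on therapy, and no deaths.

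- Counted as therapy-free throughout: the proportion on vacation at 12 months is f + (1 - f)/2 = 55-65%, and the median is 12 × log2[(1 - f)/(0.5 - f)] = 14.0-21.7 months.
- Given time zero: (1 - f)/2 = 45-35%, and the median is 12 × log2[(1 - f)/0.5] = 10.2-5.8 months.
- Excluded: 50% and 12 months.

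**The case against.** **Censoring of deaths is nowhere written.** Correct: the only censoring rule concerns loss to follow-up, so this is an inference. It is a firm one, because death is not an event in these definitions and Kaplan-Meier offers no third state.

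**An article may leave such detail to an analysis plan.** That would answer a silent article. This one names the estimator and applies it to all time-to-event outcomes. If an unseen analysis plan already treats death as a competing event, the two texts need reconciling.

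**The bias may be slight.** At 12 months, or with few deaths, it is. A median may also never be reported: at an assumed 0.08 untreatable progressions per year, the Kaplan-Meier median is ln 2/0.08 = 8.7 years. The longest possible follow-up, September 2019 to January 2026, is about 6.3 years, so the bias would then show only in the plots. This limits the size of the problem but does not remove it.

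**The covariate analyses.** A reader might infer that the Cox and log-rank analyses are also wrong. They are not. With deaths censored they address the cause-specific hazard, which is a valid target.

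**Vacation.** A reader might infer that the plan credits vacation time to patients who are under treatment throughout. The documents do not say so. A literal reading allows it, but time zero, exclusion or separate analysis are equally compatible with the text, and the data needed to identify these patients are recorded. Only the lack of a stated rule can be supported.

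**Conclusion.** The point holds for the Kaplan-Meier probabilities, plots and medians of two secondary outcomes: time to untreatable progression and systemic therapy vacation. Following the article as written would overstate the probability of the event at 36 months by about 0.5 to 16 points over the assumed grid, and by at most about 3 points at 12 months. These sizes rest on constant hazards and assumed rates; the true size depends on mortality without the event, which the article does not give. The direction does not depend on those rates: whenever deaths without the event precede later events, one minus Kaplan-Meier is too high.

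Overall, disease-free and hepatic disease-free survival, the primary outcome and the sample size are unaffected, and no confirmatory testing is planned. The point should be corrected before the final analysis but does not threaten the study's main result. The handling of patients on systemic therapy at the first ablation is a request for clarification only.

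**What to change.** For time to untreatable progression and systemic therapy vacation, replace the Kaplan-Meier estimate with the Aalen-Johansen cumulative incidence, with death as a competing event, reported with 95% confidence intervals at fixed times such as 12, 24 and 36 months. Keep Kaplan-Meier for overall, disease-free and hepatic disease-free survival. Keep the planned Cox and log-rank analyses for the two outcomes, and label them cause-specific.

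Add one sentence to the vacation definition stating how patients with systemic therapy ongoing at the first ablation are handled; for example, analyse those off therapy at that time and report the others separately.

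The cost is a few lines of text and standard R functions. Deaths are already collected for overall survival and concomitant therapy is already recorded, so no new data are needed. The downside is that the cumulative incidence may never reach 50%, in which case no median can be given and the fixed-time probabilities take its place.
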